### Measures of intervention exposure

2.6

#### Baseline and follow-up measurements [outcome]

2.6.1

Women and their partners complete the below antenatal questionnaires at baseline and late pregnancy. Where possible, validated questionnaires are used. If a validated questionnaire was not available, a self-designed questionnaire was used. The women's questionnaires include measurement of:•Breastfeeding (Attitude to breastfeeding)•Feeding Confidence•Infant Feeding Attitude•Breastfeeding Attrition Prediction Tool (BAPT) Survey•Breastfeeding Support

The support partner completes the below antenatal questionnaires at baseline and late pregnancy:•Breastfeeding (Attitude to breastfeeding)•Breastfeeding Support

Women and their partners are sent an email with a link to their questionnaires, and the researchers make a follow-up call if required to remind them to complete these.

Mothers complete a range of questionnaires at 6 weeks, 3 months, and 6 months postpartum to collect information on Feeding Details, Feeding Decision, Breastfeeding Experiences, Feeding Confidence, Infant Feeding Attitude, Breastfeeding Support, Cost Diary, Quality of Life, and Postnatal Depression.

### Intervention evaluation [process] from the participant and lactation consultant perspectives

2.7

Exit interviews will be conducted with both women and their partners (where available) to explore barriers and enablers to engaging in the intervention. The interviews will be semi-structured and the COM-B framework will be applied to the data analysis.

The normalization of the intervention into routine practice will be explored using the NOMAD questionnaire pre- and post-intervention [15]. A focus group will be conducted at the completion of the study to explore IBCLC perspectives on the sustainability of the intervention and contextual factors involved in delivery.

### Sample size

2.8

In 2017, prevalence of any breastfeeding at 3 months was 38.6% in Community Health Organisation 5 (CHO5) (SLK and WGH are within this CHO); 32.4% in CHO8 (MRH is within this CHO) and 37.3–45.7% in CHO 6, 7 and 9 (catchment area for NMH). Following our pilot study, 60–70% of women had any breastfeeding at 3 months [11]. Given that the women in this study will all have a BMI >25 (less likely to breastfeed), but will volunteer for a breastfeeding research study (more likely to breastfeed), we anticipate that the baseline breastfeeding rate within the control group would be approximately 40% at 3 months’ postpartum. This estimate is derived from a pilot study conducted in The National Maternity Hospital, Dublin from February to July 2016, and in Wexford General Hospital, Wexford from July to November 2016. We anticipate that the intervention will increase breastfeeding at 3 months to 60–70%. We based our sample size calculation on an uncorrected Pearson chi-square test of the primary hypothesis at the 0.05 level with 80% power using the PS Power and Sample Size package (CSTAR, UCD). To observe an increase in prevalence from 40 to 60%; we estimate that 194 women would be required to have 80% power to detect this effect size at a significance of 0.05, that is, 97 in each arm. To observe an increase in prevalence from 50 to 70%; we estimate that 186 women would be required to have 80% power to detect this effect size at a significance of 0.05, that is, 93 in each arm. To allow for drop outs, and allowing for the block randomisation procedure stratified by site, we calculated the required sample size will involve recruiting 220 women across the four hospital sites.

### Statistical analysis

2.9

The primary analysis of the trial will comprise of a comparison of the primary endpoint using a logistic regression model, stratified by site. A conclusion of efficacy will be determined by a statistically significant effect at a 0.05 level on the intervention coefficient. The predicted absolute probabilities of any breastfeeding, and an odds ratio for the intervention effect will be presented, overall and by site, with 95% confidence intervals. As a sensitivity analysis, a random effects logistic model will be fitted with a random intercept per site to allow for a distribution of baseline rates; however, we expect the small number of sites will be inadequate for stable or precise variance component estimates of this parameter, and it remains a secondary sensitivity analysis.

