#### Assessment of eligibility

2.2.2

Depending on the setting, electronic health records or traditional paper charts are used to screen women for eligibility in advance of women attending their antenatal appointment. Information on general sociodemographics, gestational age, reproductive history and pre- and early gestational weight gain will be obtained through interview with the participant.

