#### Intervention

2.2.8

This multi-component intervention targets prospective mothers and their support partners and spans the perinatal period from late pregnancy to six weeks’ postpartum. Intervention components include group antenatal education for prospective mothers and their support partners, individual education for new mothers in the immediate postnatal period, and professional support for new mothers to six weeks postpartum (Table 2). Women allocated to the intervention group attend a group antenatal education session usually between 28–36 weeks gestation with their support partner.

**Table 2 tbl2:** Intervention approaches used.

Approach	Description	Timing
SMS texts	Welcome to the study text with links to online questionnaires. These texts are standardised to ensure all participants received the same text. SMS texts are sent to participants in both the intervention and control groups.	Post randomisation
Email	Welcome to the study email with links to online questionnaires. Also used to send links to late pregnancy and postnatal questionnaires (6 weeks, 3 months and 6 months postpartum). These emails are standardised with all participants receiving the same email. Emails are sent to participants in both the intervention and control groups.	Throughout the study
Phone call from researcher	Researchers will phone participants to randomise them to a study group, and also to schedule the antenatal class and to give reminders about completing the online questionnaires. Phone calls from researcher to participants occur for both the intervention and control groups.	Throughout the study
Group education	Antenatal class – the antenatal class covers a range of topics in relation to breastfeeding rates, the benefits of breastfeeding, the basics of breastfeeding, and breastfeeding support. The antenatal classes are delivered by lactation consultants. Pregnant women and their support partners are required to attend the antenatal class. Intervention group only.	28–36 weeks
Individual consultation	IBCLC will provide face to face advice and support after the birth of the infant. Intervention group only.	1–3 days postpartum
Phone call from IBCLC	IBCLC will phone mother weekly to discuss her progress and issues she is having. Self-efficacy prompts. Intervention group only.	Once per week for 6 weeks postpartum

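### The primary logistic model adjusts for site only; pre-specifying maternal age and one pre-allocation prognostic score would be a cheap efficiency gain of uncertain size, not the repair of an error

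*Protocol article*

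**What the plan says.** Section 2.9 states the model: "The primary analysis of the trial will comprise of a comparison of the primary endpoint using a logistic regression model, stratified by site". The efficacy decision hangs on one term: "A conclusion of efficacy will be determined by a statistically significant effect at a 0.05 level on the intervention coefficient". For reporting, "The predicted absolute probabilities of any breastfeeding, and an odds ratio for the intervention effect will be presented, overall and by site". The only alternative model described is a sensitivity analysis with a random intercept per site. No patient-level covariate is named in either model.

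Two other sections show what is available. Section 2.2.2 says: "Information on general sociodemographics, gestational age, reproductive history and pre- and early gestational weight gain will be obtained through interview with the participant". Section 2.6.1 says: "Women and their partners complete the below antenatal questionnaires at baseline and late pregnancy". Its list for the women includes the "Breastfeeding Attrition Prediction Tool (BAPT) Survey", together with infant feeding attitude and feeding confidence.

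Timing is less clear than the baseline label suggests. The first row of Table 2 (section 2.2.8) is the "Welcome to the study text with links to online questionnaires", and its timing column places that text after randomisation. Section 2.2.6 says women are told their group once the envelope is opened and that nobody is blinded. Section 2.6.1 has the questionnaires completed through an emailed link, with a reminder call if needed.

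Section 2.8 sizes the trial on an "uncorrected Pearson chi-square test of the primary hypothesis at the 0.05 level with 80% power", that is, on an unadjusted comparison.

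**The concern.** Breastfeeding cannot be measured before birth, so a prognostic score is the nearest thing to a baseline value of the primary outcome. The plan gives reasons to expect such scores to matter. Section 2.2.8 treats attitudes and self-efficacy as the route by which the intervention works. Section 2.8 expects volunteers for a breastfeeding study to breastfeed more often. Section 2.2.1 describes a move towards self-referral during the pandemic, so motivation may vary between women.

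Leaving a truly prognostic variable out of a logistic model costs power for the treatment test and leaves chance imbalance in that variable uncorrected. With one efficacy decision on about 194 evaluable women, an inexpensive gain deserves consideration. At stake is efficiency. The validity of the test and its planned power are not in question.

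**Working it through.** **Inputs from section 2.8.** Rates 40% v 60% with 97 per arm, and 50% v 70% with 93 per arm; alpha 0.05; power 80%; recruitment target 220. Sidedness is not stated, but two-sided reproduces the figures.

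**Input from section 2.2.1.** 105 women were enrolled before 12 March 2020.

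**Assumption.** The documents do not give the correlation rho between a baseline score and breastfeeding at 3 months. It is varied from 0.2 to 0.5.

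**Step 1: reproduce the plan.** With pooled variance and no continuity correction,

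n per arm = [1.96·√(2·p̄·(1−p̄)) + 0.8416·√(p₀(1−p₀) + p₁(1−p₁))]² / (p₁−p₀)².

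- 40% v 60%: [1.96·0.7071 + 0.8416·0.6928]² / 0.04 = 1.969² / 0.04 = 96.9, so 97.
- 50% v 70%: [1.96·0.6928 + 0.8416·0.6782]² / 0.04 = 93.0, so 93.

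Both match. Power without adjustment is 80.0% at 97 per arm and 84.8% at 110 per arm.

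**Step 2: approximate power with a complete score.** Scale the variance by (1 − rho²). At 97 per arm the null standard error is √(0.50/97) = 0.0718 and the alternative standard error is √(0.48/97) = 0.0703. With k = √(1 − rho²),

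power = Φ[(0.20 − 1.96·0.0718·k) / (0.0703·k)].

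**Step 3: approximate power with half the scores missing.** Use the same formula with k = √(1 − 0.5·rho²). A half is a reasonable illustration, because 105/220 = 48% of the target had enrolled before the pandemic alone.

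**Step 4: simulation with a complete score.** 8,000 trials per value of rho, 97 per arm, one standardised covariate, marginal rates held at 40% and 60%, Wald test at 1.96.

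| rho | Odds ratio per SD | Step 2, complete | Step 4, unadjusted → adjusted | Step 3, half missing |
|---|---|---|---|---|
| 0.2 | 1.53 | 81.6% | 81.0% → 81.7% | – |
| 0.3 | 1.96 | 83.6% | 80.7% → 83.1% | 82% |
| 0.4 | 2.66 | 86.5% | 80.7% → 86.3% | 83% |
| 0.5 | 3.99 | 90.0% | 80.4% → 89.3% | 85% |

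Type I error in the simulation was 4.6% to 5.3%. Worked example for Step 3 at rho 0.4: k = √0.92 = 0.959; (0.20 − 0.1350)/0.0675 = 0.96; Φ = 83%.

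**Step 5: which quantity becomes more precise.** A second simulation (3,000 trials per cell, N = 194, 40% v 60%) kept site in both models and added the score to one. The site mix of 55/17/14/14% is assumed, with no site effect on the outcome. Simulation error is about 0.7 points for each power figure.

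| AUC of score | Power, site only → adjusted | Log odds ratio (SE), site only | Log odds ratio (SE), adjusted | SD of standardised risk difference, site only → adjusted |
|---|---|---|---|---|
| 0.50 | 80.8% → 81.0% | 0.838 (0.300) | 0.842 (0.302) | 0.071 → 0.071 |
| 0.61 | 78.8% → 80.5% | 0.834 (0.300) | 0.870 (0.309) | 0.071 → 0.070 |
| 0.70 | 78.9% → 84.4% | 0.836 (0.300) | 0.959 (0.326) | 0.072 → 0.068 |
| 0.77 | 80.0% → 88.8% | 0.839 (0.300) | 1.086 (0.351) | 0.071 → 0.063 |
| 0.82 | 80.6% → 91.9% | 0.838 (0.300) | 1.234 (0.380) | 0.071 → 0.059 |

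The standard error of the log odds ratio goes up. Power still rises because the conditional estimate moves further from zero: at AUC 0.77 the ratio of estimate to SE goes from 0.839/0.300 = 2.80 to 1.086/0.351 = 3.09. Only the standardised risk difference becomes more precise. An uninformative score costs essentially nothing.

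**The case against.** **The plan keeps its own promise.** The sample size rests on an unadjusted test, and the site-only model delivers the stated 80%. A reader might infer that the trial is underpowered or the primary test invalid; the figures support neither. Randomisation protects against imbalance in expectation, and the 5% error rate already allows for chance imbalance. This stands in full and limits the point to efficiency.

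**Covariate lists often sit in the SAP, which is not shown.** This stands in part. An SAP may add covariates, and the absence of a stated reason is weak evidence of a flaw. But the article does fix the primary model and the coefficient that decides efficacy, so that choice can be reviewed as written.

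**The scores may not be true baseline values.** A reader might infer from the baseline label in section 2.6.1 that every woman has a score taken before allocation. Table 2 does not support that: the links go out after randomisation, women know their group, and completion is not assured. Attitudes and self-efficacy are what the intervention targets, so adjusting for a score given after disclosure could bias the treatment effect. This stands, and it is why the fix admits only scores completed before disclosure.

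**The prognostic strength has no source in the documents.** This stands too. A correlation of 0.5 means an odds ratio of 3.99 per SD, and nothing in the article supports a value that high. Maternal age was not simulated, so no gain is claimed for it.

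**Adjustment does not make the odds ratio more precise.** Correct: its standard error rises and it becomes a conditional measure. A claim of greater precision holds only for the standardised risk difference.

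**Conclusion.** The point holds as a recommended, low-cost improvement. The primary model uses site alone while the trial already collects likely prognostic information. Pre-specified adjustment would raise the power of the efficacy test by between nearly nothing and about 9 points over rho 0.2 to 0.5 with complete, clean scores. If about half the women lack a usable score, the gain over 80% is about 2, 3 and 5 points at rho 0.3, 0.4 and 0.5. The lower figures are the more realistic guide, since at least 105 women enrolled before any change could apply.

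These sizes rest on an assumed correlation, one roughly normal score, and the plan's own rates and sample size. The finding that adjustment loses no power was the same in both simulations. The absence of BMI category, a randomisation stratum, from the model is a separate matter and plays no part in this conclusion.

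**What to change.** Before outcome data are analysed, amend section 2.9 as follows.

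- **Primary model.** Logistic regression with treatment, site, maternal age from the eligibility interview, and one named continuous score (the attrition tool total or the infant feeding attitude total, chosen now).
- **Which scores count.** Use a score only if the questionnaire was completed before allocation was disclosed. For women still to be enrolled, send the link at consent, ahead of the allocation call. For women already enrolled, check the questionnaire date against the date of that call. Maternal age needs no such rule because allocation cannot affect it.
- **Missing scores.** Treat all other scores as missing, with single mean imputation plus a missingness indicator, so that no woman is dropped.
- **Reporting.** Obtain the planned absolute probabilities by averaging model predictions over all women, and add the resulting risk difference with its 95% confidence interval beside the odds ratio. State that the odds ratio is conditional on the covariates.
- **Sensitivity analysis.** Keep the site-only model.

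The cost is a change of analysis wording, one further model, a date check for women already enrolled and a small shift in questionnaire timing. No extra participants or measurements are needed. The downsides are a conditional odds ratio and a reduced gain where women already enrolled contribute no usable score.

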#### Randomisation

2.2.6

Women are allocated to either intervention or control using a computer-generated scheme. Randomisation is a 1:1 allocation and stratified by study site and BMI category (CSTAR, UCD). Given the nature of the intervention, neither the participants nor the researchers are blinded to allocation. Sealed opaque envelopes will be sequentially numbered and treatment will be allocated automatically through selection of the next available envelope. Researchers select a sealed envelope in numerical order, open the envelope and will then advise the woman of the group they have been allocated to. Women receive a phone call after they have provided consent to take part in the study.

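### Randomisation is stratified by site and BMI category, but the primary and sensitivity models carry site only, which forgoes a small, free gain in power

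*Protocol article*

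**What the plan says.** Three sections of the protocol article bear on this point.

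- Randomisation (2.2.6): "Randomisation is a 1:1 allocation and stratified by study site and BMI category".
- Sample size (2.8), explaining the increase to 220 women: "allowing for the block randomisation procedure stratified by site". BMI category is not named.
- Statistical analysis (2.9): the primary analysis is a "comparison of the primary endpoint using a logistic regression model, stratified by site". Efficacy is judged by a "statistically significant effect at a 0.05 level on the intervention coefficient". For sensitivity, "a random effects logistic model will be fitted with a random intercept per site". BMI category is in neither model.

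The inclusion criteria (2.2.3) require a BMI of at least 25 at the first antenatal visit, so the value needed to form the category exists for every woman before allocation.

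**The concern.** A factor used to stratify randomisation is normally carried into the primary model. Stratification makes the arms more alike on that factor than chance would. If the factor predicts the outcome, the treatment comparison varies less from trial to trial than a model without the factor assumes. The test is then somewhat conservative and some power is given away.

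Section 2.9 names one of the two factors and hangs the efficacy conclusion on the intervention coefficient of that model. It therefore states a choice that does not match section 2.2.6, rather than leaving a detail open. Section 2.8 adds doubt about which scheme was used, since it mentions site alone. At stake are a little power in a trial sized at 80%, and a clear link between the allocation scheme and the analysis.

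**Working it through.** **1. The plan's own figures.** Section 2.8 uses an "uncorrected Pearson chi-square test of the primary hypothesis at the 0.05 level with 80% power". With two-sided alpha 0.05, per-arm n = [1.960·√(2p̄(1−p̄)) + 0.8416·√(p₁(1−p₁)+p₂(1−p₂))]² / (p₂−p₁)².

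- 40% vs 60%: p̄ = 0.5; [1.960·√0.50 + 0.8416·√0.48]² / 0.04 = (1.386 + 0.583)² / 0.04 ≈ 96.9, so 97 per arm and 194 in total. The plan says "To observe an increase in prevalence from 40 to 60%; we estimate that 194 women would be required", which agrees.
- 50% vs 70%: p̄ = 0.6; [1.960·√0.48 + 0.8416·√0.46]² / 0.04 = (1.358 + 0.571)² / 0.04 ≈ 93.0, so 93 per arm and 186 in total. This also agrees.

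Neither calculation involves strata, so the stated sizes do not depend on the point.

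**2. Effect of leaving BMI category out.** From the documents: N=194, 1:1 allocation, four sites, stratification by site and BMI category, and rates of 40% vs 60% (or 40% vs 40% for type I error). Assumed, because the article does not give them: two BMI categories with 40% of women in the higher one, blocks of 4, site shares 40/20/20/20, small site differences (logit offsets +0.10, +0.05, +0.05, −0.20), site fitted as fixed effects, and the BMI odds ratio, varied from 1 to 0.24.

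Outcome model: logit P(breastfeeding) = a(arm) + site offset + ln(BMI odds ratio) × higher category. The arm intercepts were solved so that the overall rates stayed at the planned values. There were 4,000 replicates per scenario, with two-sided Wald tests at 0.05.

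| BMI odds ratio | Type I: site | Type I: site+BMI | Power: site | Power: site+BMI | Gain (points) | Mean log OR: site | Mean log OR: site+BMI |
|---|---|---|---|---|---|---|---|
| 1 | 4.6% | 4.7% | 80.9% | 80.9% | 0.0 | 0.84 | 0.85 |
| 0.67 | 4.8% | 4.8% | 81.6% | 82.1% | 0.5 | 0.84 | 0.85 |
| 0.5 | 4.1% | 4.3% | 81.1% | 81.8% | 0.7 | 0.83 | 0.86 |
| 0.33 | 4.7% | 5.6% | 81.4% | 82.9% | 1.5 | 0.83 | 0.90 |
| 0.24 | 4.1% | 5.3% | 82.9% | 85.1% | 2.2 | 0.84 | 0.95 |

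Monte Carlo standard error: √(0.05×0.95/4000) ≈ 0.3 points for type I error and √(0.8×0.2/4000) ≈ 0.6 points for power. Both models were fitted to the same data sets, so the gains are more precise than the separate powers.

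**3. Sensitivity to the set-up.** Holding the conditional log odds ratio fixed, instead of the overall rates, gives a similar picture.

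- N=194, conditional log OR 0.85: power 80.6% vs 81.6% at a BMI log odds ratio of −1.0, and a negligible difference at −0.5. At −1.5 (odds ratio e^−1.5 ≈ 0.22), the most extreme case tried, power is 74.5% vs 78.5%, a gap of 4 points.
- N=200, conditional log OR 0.81: power 77.0% vs 78.3% at −1.0, and less than 1 point apart at −0.5.

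**4. Standard errors.** At N=200 and a BMI log odds ratio of −1.0, the site-only model's mean standard error was 0.293 against an empirical SD of 0.282 for its own estimate: 0.293/0.282 ≈ 1.04, about 4% too large. The BMI-adjusted model's mean standard error was 0.304, larger still. At −0.5 the site-only figures were 0.294 against 0.303, so there was no overstatement.

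**The case against.** The strongest case against is size. Type I error under the site-only model stays at or just below 5%, so a false claim of efficacy is not made more likely, and the power at issue is mostly a point or two. That stands, and it sets the weight of the point.

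The second objection is that the documents give no BMI gradient inside the trial. The Introduction and section 2.8 contrast women with raised BMI against women with healthy BMI, while every participant has a BMI of at least 25, and the article does not define the categories. That stands too. If the gradient is nil, the loss is nil (first row of the table).

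The third is that section 2.8 mentions site in passing and does not say that site was the only factor. That also stands. The documents cannot show which section describes the scheme in use, so section 2.8 should not be presumed wrong.

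What does not stand is an appeal to an unseen analysis plan. Section 2.9 states the model and names its stratifier.

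Three stronger readings are tempting but unsupported:

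- **The site-only odds ratio is biased.** It is not. With overall rates held at 40% and 60%, its mean log odds ratio stays at 0.83 to 0.84 whatever the BMI effect, and only the BMI-conditional figure rises. That is non-collapsibility: two valid quantities, one averaged over BMI and one conditional on it.
- **Adding BMI category narrows the confidence interval for the log odds ratio.** It does not. The nominal standard error goes up slightly, and the power gain comes through the larger coefficient.
- **The omission calls for wider changes to the analysis**, such as a risk difference, a stated direction of effect or models for secondary outcomes. None of these follows from an omitted stratification factor, and section 2.9 already promises predicted absolute probabilities with 95% intervals.

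**Conclusion.** The mismatch is real and lies in the article's own text: two stratification factors at randomisation, one in each model, and one in the description of the blocks. Its consequence is small to modest. At N=194 the site-only test gives up about 0 to 2 points of power for assumed BMI odds ratios of 1 to 0.24, and 4 points in the most extreme case examined. It is at worst slightly conservative. The validity of the trial and the stated 194 and 186 are untouched.

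The size rests on assumptions that the documents do not supply: the BMI effect within this population above all, and also two categories, a 40% share in the higher one, blocks of 4 and the spread across sites. This is an improvement worth making, not a must-fix.

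**What to change.** - In section 2.9, specify the primary analysis as a logistic regression with fixed effects for intervention, study site and BMI category, using the categories applied at randomisation.
- Add BMI category as a fixed effect to the random-intercept sensitivity model.
- Reconcile sections 2.2.6 and 2.8 against the allocation scheme as generated. If both factors were used, name both in section 2.8. If BMI category was not used, correct section 2.2.6; the site-only model then matches the design.

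The cost is a sentence or two and one model term per BMI category beyond the first. No new data are needed and the sample size does not change. Make the change before outcomes are compared by arm, because a covariate added afterwards would look data-driven.
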